### Data access and confidentiality

4.4

Only the principal investigator and authorized statisticians will have access to the final de-identified dataset. All personal identifiers will be stored separately from research data in a password-protected, encrypted database. No contractual agreements limit access to the data for investigators.

### Dissemination policy

4.5

The results of this study will be submitted for publication in peer-reviewed journals and presented at national and international conferences. The findings will be shared with participants via a plain-language summary distributed through the clinical team upon request. There are no publication restrictions.

## Discussion

5

One of the potential strengths of this study is its ability to explore the multiple pathways through which a virtual reality-based intervention may influence depressive symptoms in adolescents. Although the precise mechanisms remain to be fully elucidated, several complementary processes may contribute to the therapeutic effects. First, the intervention incorporates interactive task-oriented activities and goal-directed engagement within an immersive virtual environment. These features may promote behavioral activation, a well-established therapeutic principle in depression treatment. By encouraging active participation, task completion, and positive reinforcement, the intervention may help counteract the withdrawal, reduced activity, and diminished motivation commonly observed in depressed adolescents. Second, the immersive nature of virtual reality may facilitate emotion regulation. Relaxation-oriented environments, such as underwater and forest landscapes, are designed to reduce psychological stress and provide opportunities for emotional soothing. Furthermore, guided interactions with virtual companions may enhance adaptive emotional processing and reduce negative emotional reactivity. Improvements in these processes may be reflected in reductions in depressive and anxiety symptoms as measured by the HAMD-24, CDI, and HAMA-14. Third, the intervention may influence cognitive functioning by engaging participants in sustained attention, problem-solving, and interactive decision-making tasks embedded within the virtual scenarios. Previous research has shown that adolescents with depression often exhibit impairments in attention, executive function, and cognitive flexibility. By involving participants in structured cognitive activities, the VR intervention may help improve cognitive performance, an aspect that will be explored through the MoCA. Finally, virtual reality may exert physiological regulatory effects by modulating autonomic nervous system activity. According to the neurovisceral integration model, depression is associated with impaired autonomic flexibility and reduced heart rate variability. Immersive relaxation experiences may reduce stress-related sympathetic activation and promote parasympathetic recovery, potentially leading to improvements in HRV indices. Thus, the inclusion of heart rate variability measurement offers an opportunity to examine whether psychological improvements are accompanied by objective changes in autonomic regulation.

Recent research further suggests that the therapeutic value of virtual reality may extend beyond symptomatic distraction to involve broader psychological and physiological regulatory processes. For example, studies have reported that (Wei et al., 2026) VR-based exercise and extreme sports interventions can improve emotional well-being, reduce perceived stress, and enhance psychological resilience in vulnerable adolescent populations. Similarly, immersive VR experiences have been associated with reduced anxiety and stress responses in individuals with social anxiety disorder (Wang Z. et al., 2025). These findings indicate that virtual environments may promote psychological adaptation through active engagement, experiential learning, and positive emotional experiences, rather than merely passive observation. Although the intervention in this study differs from VR-based exercise and extreme sports paradigms, several underlying mechanisms may be shared. Both approaches rely on immersive engagement, interactive participation, and the provision of novel experiences that may temporarily divert attention from maladaptive cognitive patterns while encouraging adaptive emotional processing. For adolescents with depression, who often exhibit reduced motivation, social withdrawal, and persistent negative self-focused thinking, such immersive, goal-oriented experiences may facilitate behavioral activation and emotional engagement, thereby contributing to symptom improvement. From a broader public health perspective, emerging evidence supports VR-based interventions as an accessible and engaging non-pharmacological approach with the potential to promote mental health and alleviate psychological distress (Wang L. et al., 2025). Compared with these previous studies, the present study differs in several important respects. First, it specifically focuses on adolescents with a clinical diagnosis of major depressive disorder, a population that remains understudied in VR intervention research. Second, the intervention in this study combines immersive relaxation environments with interactive tasks designed to promote emotion regulation and behavioral engagement. Third, the study includes not only symptom-based assessments but also cognitive and physiological outcome measures, thereby allowing for the exploration of potential mechanisms underlying treatment effects. By integrating affective, cognitive, and autonomic outcome domains within a randomized controlled design, this study may contribute to a more comprehensive understanding of how VR interventions affect adolescent depression.

This study also has several limitations. First, it is a single-center study with a relatively limited sample size, which may affect the generalizability of the findings. Second, due to the nature of the intervention, complete blinding of participants is difficult to achieve, and non-specific effects may be present. Third, an active control condition was not included. The control group received usual care, while the intervention group received usual care plus the VR intervention. Therefore, the observed between-group differences cannot be attributed solely to the immersive VR technology itself, but may also be influenced by factors such as increased engagement, novelty effects, expectancy effects, or more frequent interactions with research staff. Future studies incorporating an active control condition, such as a non-immersive digital intervention or an alternative psychosocial activity, would help clarify the specific effects of immersive VR technology. Fourth, the study included participants aged 10–19 years, covering a relatively broad developmental period. Adolescence is characterized by significant cognitive, emotional, and neurobiological changes, and the effects of the VR intervention may vary across developmental stages. Although randomization can balance age distribution between groups, the current sample size does not provide sufficient power for well-powered subgroup analyses. Therefore, age-related heterogeneity should be considered when interpreting the results. Fifth, although the VR intervention was delivered according to a standardized protocol, no formal treatment fidelity assessment was conducted. Differences in engagement, intervention adherence, or implementation consistency may not have been fully captured. Future studies should consider incorporating structured monitoring procedures, such as intervention checklists, session completion records, and independent fidelity ratings, to further strengthen internal validity.

Finally, participants will be followed up for 3 months after the intervention, with follow-up assessments conducted at 1, 2, and 3 months after discharge. The primary aim of the follow-up is to assess the short- to intermediate-term maintenance of treatment effects on depressive symptoms, autonomic function, cognitive function, and related psychological outcomes. The three-month follow-up period was chosen based on both methodological and practical considerations. On the one hand, this study aims to examine the immediate, short-term, and intermediate-term effects of the VR intervention rather than long-term relapse prevention. On the other hand, the study population consists of hospitalized adolescents with depression; longer follow-up periods may be associated with increased dropout rates as participants return to school or community settings after discharge. Therefore, this study is not intended to determine long-term sustainability of treatment effects, relapse rates, or relapse prevention outcomes beyond the three-month observation period. Any benefits observed during the 3-month follow-up should be interpreted as evidence of short- to intermediate-term maintenance rather than long-term efficacy. Future studies with longer follow-up periods (e.g., 6–12 months) are needed to assess the durability of treatment effects and their potential impact on relapse prevention.

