**Methods:**

Protocol version 1.0, January 2026. This study is designed as a single-center, parallel-group randomized controlled trial. A total of 72 adolescents with depressive disorder who meet the eligibility criteria will be recruited and randomly assigned in a 1:1 ratio to either the intervention group or the control group. Participants in the control group will receive usual care, while those in the intervention group will receive additional VR-based intervention for 4 weeks (three sessions per week, approximately 25 min per session). Assessments will be conducted at baseline (T0), post-intervention (T1), and follow-up (T2). The primary outcome is the change in the 24-item Hamilton Depression Rating Scale (HAMD-24) score from T0 to T1. Secondary outcomes include the Hamilton Anxiety Rating Scale-14 (HAMA-14), Children’s Depression Inventory (CDI), Montreal Cognitive Assessment (MoCA), and heart rate variability (HRV) parameters (SDNN, RMSSD, LF, HF, and LF/HF). Data will be analyzed using linear mixed-effects models under the intention-to-treat principle.

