### Study design

3.1

This study is a single-center, parallel-group randomized controlled trial designed to evaluate the clinical effectiveness of a virtual reality (VR)–based intervention in adolescents with depressive disorder. Eligible participants will be randomly assigned in a 1:1 ratio to either the intervention group or the control group.

Assessments will be conducted at baseline (T0), immediately after the intervention (T1), and at follow-up (T2). The study protocol has been developed in accordance with the SPIRIT (Standard Protocol Items: Recommendations for Interventional Trials) guidelines (Figure 1).

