#### Control group

3.6.1

Participants in the control group will receive standard inpatient psychiatric care as provided by the Department of Child and Adolescent Psychiatry. Standard care includes pharmacological treatment prescribed by the attending psychiatrist, routine nursing care, symptom monitoring, safety assessments, medication management, and supportive communication as part of usual inpatient care. Pharmacological treatment will be adjusted by the attending psychiatrist based on clinical needs and will not be influenced by the research team.

Supportive communication is routinely provided by psychiatrists and psychiatric nurses during daily clinical interactions, with an emphasis on emotional support, treatment adherence, encouragement of coping skills, and risk assessment. However, participants will not receive any structured psychological therapy during the study period. To minimize potential confounding factors, both groups will receive the same standard inpatient psychiatric care throughout the study. The only difference between the two groups is that participants in the intervention group will additionally receive a virtual reality-based intervention. Standardized case report forms will be used to document medication use, medication adjustments, psychiatric consultations, and other clinically relevant interventions during the study period in order to monitor treatment exposure and potential co-interventions.

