### Outcomes

3.7

The primary outcome of this study is the change in the 24-item Hamilton Depression Rating Scale (HAMD-24) (Wiebe et al., 2022) score from baseline (T0) to post-intervention (T1). Assessments will be conducted by trained evaluators who are blinded to group allocation.

Secondary outcomes include: 1. Anxiety symptoms, assessed using the Hamilton Anxiety Rating Scale-14 (HAMA-14) (Li Y. et al., 2025); 2. Self-reported depressive symptoms (Li X. et al., 2025), assessed using the Children’s Depression Inventory (CDI); 3. Cognitive function (Jia et al., 2021), assessed using the Montreal Cognitive Assessment (MoCA). All psychological assessments will be conducted at baseline (T0), post-intervention (T1), and follow-up (T2). 4. Heart rate variability (HRV) parameters (Shapiro et al., 2007; Kircanski et al., 2019), including SDNN, RMSSD, low-frequency power (LF), high-frequency power (HF), and the LF/HF ratio, will be measured as objective physiological outcomes. Electrocardiogram signals will be recorded for at least 5 min under resting conditions in a quiet environment, and both time-domain and frequency-domain analyses will be performed.

Although the HAMD was originally developed for adults, it has been widely used in clinical studies involving adolescents with major depressive disorder and has demonstrated acceptable reliability and validity in adolescent populations (Zhao et al., 2023). Previous studies have shown that HAMD scores are significantly correlated with other well-established measures of depression severity in adolescents, supporting its clinical utility in assessing symptom severity and treatment response (Croarkin et al., 2021; Li et al., 2023). The HAMD is routinely used in psychiatric clinical practice, and our team has extensive experience in its administration. The scale has good sensitivity to symptom change and facilitates comparisons with previous depression trials. To enhance the assessment of depressive symptoms and address potential developmental limitations, the CDI—a developmentally appropriate self-report measure for children and adolescents—will also be administered at all assessment time points. The combined use of a clinician-rated scale and a self-report measure is expected to provide a more comprehensive assessment of the severity of depressive symptoms.

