### Data collection and assessment schedule

3.8

Participants will be recruited from the Department of Psychiatry at the Affiliated Hospital of Henan Medical University. During the initial screening phase, potential participants and their legal guardians will be provided with detailed information about the study. Eligibility will be preliminarily assessed based on age, confirmed diagnosis of depressive disorder, and the absence of major physical illnesses or a history of epilepsy.

Participants who pass the preliminary screening will be invited to attend a face-to-face interview to further verify the inclusion and exclusion criteria. Written informed consent will be obtained from both participants and their legal guardians prior to enrollment.

Eligible participants will then be enrolled in the study and undergo baseline assessment (T0), followed by post-intervention assessment (T1) and follow-up assessment (T2). The detailed schedule of data collection is presented in Table 1.

**Table 1 tab1:** Timeline of data collection.

Item	Recruitment	Pre-treatment (TO)	Post-treatment (T1)	Follow-up (T2)
Screening	×			
Demographics	×			
Medical history	×			
Informed consent	×			
Randomization		×		
HRV		×	×	×
HAMD-24		×	×	×
HAMA-14		×	×	×
CDI		×	×	×
MoCA		×	×	×

HRV, Heart Rate Variability; HAMD-24, Hamilton Depression Rating Scale, 24-item; HAMA-14, Hamilton Anxiety Rating Scale, 14-item; CDI, Children’s Depression Inventory; MoCA, Montreal Cognitive Assessment.

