### Statistical analysis

3.11

All statistical analyses will be performed using SPSS (version 26.0), with two-sided tests and a significance level set at *p* < 0.05. Baseline characteristics will be summarized using descriptive statistics. Continuous variables will be presented as mean ± standard deviation (SD) or median (interquartile range), depending on the data distribution, while categorical variables will be expressed as frequencies and percentages. Comparability of baseline characteristics between groups will be assessed using independent-samples *t*-tests, Mann–Whitney *U* tests, chi-square tests, or Fisher’s exact tests, as appropriate.

The primary outcome measure (HAMD-24 score) will be analyzed using linear mixed-effects models (LMM) to account for repeated measurements over time. Treatment group (intervention vs. control), time (T0, T1, and T2), and the group-by-time interaction will be specified as fixed effects. A subject-specific random intercept will be included as a random effect to account for within-subject correlations across repeated assessments. The group-by-time interaction will be considered the main parameter of interest for evaluating the intervention effect. Baseline values of the corresponding outcome measure will be included as covariates in the model to improve statistical precision and control for potential baseline differences. Estimated marginal means, mean differences, 95% confidence intervals, and associated *p*-values will be reported.

Secondary outcome measures, including the HAMA-14, CDI, MoCA, and HRV indices, will be analyzed using similar linear mixed-effects models. Given the exploratory nature of these secondary outcomes, the results will be interpreted with caution and considered hypothesis-generating.

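### The Methods plan one follow-up assessment (T2) and the Discussion plans three, counted from two different origins; nothing says which visit is T2, yet the interaction named as the main parameter spans it

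*Protocol article*

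**What the plan says.** **One follow-up.** The Abstract (Methods) states: "Assessments will be conducted at baseline (T0), post-intervention (T1), and follow-up (T2". Section 3.1 has the same three occasions: "Assessments will be conducted at baseline (T0), immediately after the intervention (T1), and at follow-up (T2". Section 3.7 repeats them for the psychological scales: "All psychological assessments will be conducted at baseline (T0), post-intervention (T1), and follow-up (T2". Section 3.8 describes baseline "followed by post-intervention assessment (T1) and follow-up assessment (T2", and Table 1 has a single follow-up column in which HRV, HAMD-24, HAMA-14, CDI and MoCA are each marked once. In section 3.11 the model has "time (T0, T1, and T2), and the group-by-time interaction will be specified as fixed effects", and the interaction is named as the main parameter of interest. None of these places attaches a date or a time origin to T2.

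**Three follow-ups.** The last paragraph of the Discussion says that "participants will be followed up for 3 months after the intervention, with follow-up assessments conducted at 1, 2, and 3 months after discharge". It gives these visits an aim of their own: maintenance of effects on depressive symptoms, autonomic function, cognition and related psychological outcomes.

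**The concern.** Both schedules are current, forward-looking statements of the plan, and they cannot both be followed. Staff working from Table 1 would assess each participant once after T1; staff working from the Discussion would do so three times.

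Three things are at stake in the analysis.

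- The model has one level for follow-up. If three visits take place, either two go unused or one is picked to serve as T2, and no rule is given for picking it. The pick could be made with the data in view.
- The parameter of interest is the interaction over all levels of time, so the number of follow-ups changes what is tested.
- The imputation model in section 3.10's successor on analysis (section 3.11) draws on the follow-up measurements that are available, and that set differs between the two schedules.

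The time origin adds a separate difficulty. Discharge occurs after randomisation. Sessions are given in hospital over 4 weeks in one arm only, so discharge timing may differ by arm. Visits timed from discharge could then fall at different intervals since randomisation in the two arms.

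**Working it through.** **1. Is the planned sample size touched?** Inputs from section 3.4: difference 4.34, SD about 5.21, two-sided alpha 0.05, power 90%, dropout 10%.

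- SD check: sqrt((5.03² + 5.39²)/2) = 5.213.
- Normal approximation: n = 2 × [5.21 × (1.960 + 1.282)/4.34]² = 30.28, rounded up to 31 per group.
- Exact t calculation: power is 0.8974 at n = 31 and 0.9066 at n = 32, so 32 per group, as stated.
- Dropout: 32/0.90 = 35.6, rounded up to 36 per group, 72 in total, as stated.

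The plan's figures reproduce. They rest on one post-intervention comparison, so follow-up timing does not enter.

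**2. Is the primary endpoint touched?** It is the HAMD-24 change from T0 to T1 (Abstract, section 3.7). T1 falls immediately after the intervention (section 3.1). No follow-up visit enters its definition.

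**3. Is the named parameter touched?** With two groups and k categorical occasions, the interaction has (2 − 1) × (k − 1) degrees of freedom.

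| Source | Occasions | k | Interaction df |
|---|---|---|---|
| Abstract, 3.1, 3.7, 3.8, Table 1, 3.11 | T0, T1, T2 | 3 | 2 |
| Discussion, all visits modelled | T0, T1, months 1, 2, 3 | 5 | 4 |

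Only one of these components, the group difference in change from T0 to T1, is the primary endpoint. The rest, one or three of them, concern follow-up. A joint test of the interaction therefore depends on the schedule although the endpoint does not.

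**4. Can the two schedules be read as one?**

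- *T2 as a label for all three visits.* This does not fit a single Table 1 column or a model with "time (T0, T1, and T2" as its levels.
- *T2 as the 3-month visit.* This is possible, but no section says so, and the 1- and 2-month visits would still be absent from the schedule and the model.
- *Discharge as the same day as the end of the intervention.* This would merge the two origins, but no section ties discharge to the end of the 4 weeks.

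**5. Where does the conflict of origins lie?** Inside the Discussion sentence alone. The Methods give T2 no origin, so they neither contradict nor settle it.

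**The case against.** The strongest reply is that the main result is safe: the endpoint is T0 to T1, the sample size is built on a post-intervention difference, and secondary outcomes are declared exploratory. This stands for the endpoint and the sample size. It does not stand for the primary analysis as worded, because section 3.11 points to the interaction and not to the T0-to-T1 contrast.

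A second reply is that an article may leave visit dates and windows to the full protocol, and that Figure 1 is not shown. This also stands: an undated T2 would not by itself be a fault. What remains is a conflict between printed statements on the number of visits, and between two origins in one sentence.

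Three stronger readings are tempting, and the documents do not support them.

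- *That the T2 difference is biased by a calculable amount.* This would need the difference in discharge timing between arms and the rate at which HAMD-24 is still changing after treatment. Neither is given, and zero is possible for both. The planned 4.34 points is a post-intervention difference and is no yardstick for T2. Arm-dependent discharge is a risk, not a documented fact.
- *That maintenance has no analysis at all.* The model does contain a T2 level, so a group contrast at T2 exists. What is missing is which visit supplies it and what becomes of the others.
- *That section 3.6.1 adds a second contradiction* by stating that "both groups will receive the same standard inpatient psychiatric care throughout the study" while follow-up comes after discharge. That sentence is about equal co-treatment in the two arms and adds little to the schedule conflict.

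**Conclusion.** The contradiction is real, and nothing in the article resolves it: one follow-up against three, two time origins within one sentence, and no visit identified as T2. In size, it is 3 against 5 assessment occasions and 2 against 4 degrees of freedom for the interaction named as the main parameter of interest. The 4 assumes that all visits would be modelled as separate categorical levels of time.

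The T0-to-T1 endpoint and the sample size of 72 are unaffected. The maintenance aim is exposed to choosing the visit after the data are seen. Unequal time since randomisation under discharge-based visits is a possibility to design out; the documents give no basis for putting a number on it.

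**What to change.** Reconcile the Abstract, sections 3.1, 3.7, 3.8 with Table 1, 3.11 and the last paragraph of the Discussion to one schedule:

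1. One list of visits with one time origin that does not depend on discharge. Either randomisation or the scheduled end of the 4-week period would do, applied equally in both arms.
2. Name, before follow-up data are seen, which visit is T2 for the maintenance contrast.
3. Either add the 1- and 2-month visits to Table 1 and as levels of time in the model, or remove them from the Discussion.
4. State the group contrast in change from T0 to T1, estimated from the model, as the primary test, so that it does not depend on how many follow-ups there are.
5. Record the discharge date, so that any difference in its timing between arms can be described.

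Cost: more than wording. Section 4.1 requires amendments to be approved by both ethics committees before they take effect, and some visits move from discharge-based to fixed dates. The sample size does not change. The change is cheap before follow-up data are seen and hard to defend afterwards.
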